### Data collection

Baseline and follow-up data will be collected at 0 and 12 months respectively using an anonymous online iPad-Mini-based survey. This method was chosen in consultation with Victoria Police, and was informed by a number of considerations. First, identifying information is not usually requested in internal surveys (which average 20–25 % response), and when they do, respondents often leave the field/s blank. It was also anticipated that members would be especially reluctant to include identifying information on a survey that includes questions about mental health. Hence we decided to forgo the collection of identifying information, greatly limiting analysis possibilities, in order to optimise response rates and representativeness in the survey data. It was not possible to use incentives due to Victoria Police anti-corruption policies.

To further address concerns about confidentiality, we will use an electronic survey method that is independent of Victoria Police IT systems. The iPads are clearly marked as Deakin University property, and anonymity and independence from the host organisation’s IT systems will be emphasised in information sessions and promotion activities, alongside information on the voluntary nature of the survey on the welcome page. One or two iPads will be left at each participating station over a period of two to three weeks, during which time the number of responses will be monitored by the researchers on the university server to which the survey data is sent. Response rate updates will be sent to the station ‘champion’ who will help promote survey participation at the stations, and will be complemented by project field staff visits timed to coincide with shift changes to promote the survey.

Individual-level survey data will be complemented by station-level data collected from station command and relevant departments (e.g., HR), and will include staffing levels, changes in key staff at participating stations, restructures, and other events or activities that could affect intervention outcomes. Finally, qualitative interview data will also be collected as detailed below.

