#### Employment information

Current job title and rank, time in current position, length of employment in Victoria Police, full- versus part-time.

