### Analysis

The following main hypotheses on intervention effectiveness will be tested comparing the intervention versus the control sites at the cluster level based on cluster-wide survey responses:There will be significantly greater improvement in the intervention compared to wait-list control arms in the primary outcomes of mental health literacy and psychosocial working conditions over a one year period;There will be significantly greater improvement in the intervention versus control arms in the secondary outcomes of mental health and organisational outcomes over a one year period;

Analyses will be conducted following CONSORT guidelines for cluster-randomised trials [69]. Because we are not collecting individual identifier information, within-person analyses over time are not possible. A simple two-stage analysis approach will be used: summary measures (e.g., means) will be generated by cluster for pre- and post-intervention, and pre- and post-intervention values will be subtracted to give the mean change by cluster, followed by a two-sample test comparing the summary measures by arm (e.g., t-test, where *n* = total number of clusters). Cluster summaries will be based on census surveys within each station, with all respondents included regardless of whether they participating in intervention activities or not. We will additionally adjust for variation in cluster (station) size by weighting by the number of individuals per cluster. Pending the results of process evaluation, further analyses may be conducted to explore the influence of intervention fidelity and reach, or to attempt to account for activities at control stations that may have influenced outcomes.

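### Changes in unadjusted station means from two unlinked survey waves are open to a modest bias if respondent mix shifts differently by arm, although rank, sex, age group and length of employment are collected and could be adjusted for

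*Protocol article*

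**What the plan says.** The Analysis section sets out a two-stage method. In stage 1, "summary measures (e.g., means) will be generated by cluster for pre- and post-intervention". A difference is then taken for each station: "pre- and post-intervention values will be subtracted to give the mean change by cluster". In stage 2, the station changes are compared by arm in a two-sample test whose sample size is the number of stations. On who is counted: "Cluster summaries will be based on census surveys within each station, with all respondents included". The one adjustment named is: "We will additionally adjust for variation in cluster (station) size by weighting by the number of individuals per cluster". Beyond that, "further analyses may be conducted to explore the influence of intervention fidelity and reach", or to account for activities at control stations. Respondent mix is not mentioned. The Abstract describes the same plan.

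The reason given for this simple method is anonymity. Data collection says: "Hence we decided to forgo the collection of identifying information, greatly limiting analysis possibilities". The Analysis section adds: "Because we are not collecting individual identifier information, within-person analyses over time are not possible".

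The survey nevertheless records respondent characteristics. Employment information lists "Current job title and rank, time in current position, length of employment in Victoria Police, full- versus part-time", and Socio-demographics lists age group, sex and education. The section on wait-list control sites says that both arms receive the same baseline and final assessments.

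**The concern.** Anonymity rules out following a person from one wave to the next. It does not rule out adjusting each wave for the characteristics its respondents report. The plan gives up the first for a stated reason and leaves the second unused without one.

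Four features of the trial make this relevant:

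- **Incomplete response.** The survey is meant as a census, but Trial status reports first-stratum baseline response of about 70%, from 53 to 88% by station. Each wave is therefore a different partial sample of the station.
- **Timing of allocation.** Stations are randomised after the baseline survey and cannot be blinded afterwards. Arm can influence who answers at follow-up but not who answered at baseline.
- **Unequal contact by rank.** Leaders in intervention stations receive a 360° debrief, workshops and up to four hours of coaching. Control stations receive no project activity. A response change specific to one rank group and one arm is possible.
- **Rank may matter for the outcome.** The development interviews suggested better mental health literacy among senior members. Randomisation is balanced on the junior-to-senior ratio, but that ratio describes the roster, not who responds at 12 months.

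If the leader share of respondents changes more in one arm, part of the difference in mean change reflects composition and not effect. With 24 stations in the test, random changes in mix also add some noise.

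**Working it through.** **1. The planning target.** In Table 1, mental health knowledge has a difference of 1.79 and an SD of 3.57, so the target is 1.79 / 3.57 = 0.50 SD. The normal-approximation formula at two-sided alpha 0.05 and power 0.90 gives 84 per arm, as stated. The design effect is 1 + 19 × 0.05 = 1.95, and 84 × 1.95 = 163.8, i.e. 164. Then 164 / 0.70 = 234.3 and 234 / 20 = 11.7, i.e. 12 stations per arm. The plan's figures reproduce and are not affected by this point.

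**2. Inputs for the bias.**
- From the documents: response of about 70% (range 53 to 88%), 12 stations per arm, m = 20, ICC 0.05.
- Assumed: leaders are 20% of the station; baseline response is equal across ranks; the leader-junior gap is 0.5 to 1.0 SD; the between-wave correlation of station means is 0.5.

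**3. How far the leader share can move.** With leader response L and junior response J,

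share = 0.20 L / (0.20 L + 0.80 J).

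| L | J | Leader share | Change from 20% |
|---|---|---|---|
| 70% | 70% | 20.0% | 0 |
| 85% | 70% | 0.17 / 0.73 = 23.3% | 3.3 points |
| 100% | 70% | 0.20 / 0.76 = 26.3% | 6.3 points |
| 100% | 53% | 0.20 / 0.624 = 32.1% | 12.1 points |
| 100% | 88% | 0.20 / 0.904 = 22.1% | 2.1 points |

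The last two rows start from the lowest and highest station response seen at baseline.

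**4. Bias.** Bias = (difference between arms in the change of leader share) × (rank gap in SD). At 70% baseline response, with the change confined to leaders in one arm:

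- Leaders 70% to 85%: 0.033 × 0.5 = 0.016 SD; 0.033 × 1.0 = 0.033 SD.
- Leaders 70% to 100%: 0.063 × 0.5 = 0.032 SD; 0.063 × 1.0 = 0.063 SD.

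The range is about 0.02 to 0.06 SD, or 3 to 13% of the 0.50 SD target. An equal change in both arms gives a bias of 0.

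**5. Effect on the test.** The variance of a station change is 2 × [0.05 × (1 − 0.5) + 0.95 / 20] = 0.145. The standard error of the contrast is √(2 × 0.145 / 12) = 0.155 SD. From the non-central t with 22 df, a bias of 0.016 SD gives a two-sided type I error of 5.1%, and 0.063 SD gives 6.7%, against a nominal 5%.

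**6. Precision.** Rank explains roughly 0.2 × 0.8 × gap² = 0.04 to 0.16 of within-station variance. Only the sampling part of the station-change variance shrinks: 0.0475 of 0.0725 before doubling. The variance falls by 0.04 × 0.0475 / 0.0725 = 2.6% to 0.16 × 0.0475 / 0.0725 = 10.5%. The standard error falls by 1.3 to 5.4%.

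**The case against.** The strongest objection concerns size. A reader might infer a shift of 15 points or more in the leader share, and so a bias of 15 to 30% of the target (0.15 × 0.5 = 0.075 SD to 0.15 × 1.0 = 0.15 SD). The documents do not support that. At 70% response and a 20% leader share, full response from leaders yields only 6.3 points, and no leader share allows more than about 9. To reach 15 points with every intervention leader answering, junior response in intervention stations would also have to fall to about 46%, or control leaders' response to about 36%. The 53 to 88% range is variation between stations at one baseline wave; it is not evidence that the mix changes between waves or arms. This objection stands, and the smaller figures above reflect it.

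A reader might also infer that any change in who answers is taken for an effect. It is not: a change common to both arms cancels.

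The link between rank and outcome is thinly documented. It rests on interviews with 5 junior and 13 senior members, and for literacy only. The gap is therefore an assumption. The measure for Sergeants and above cannot be biased by the leader-junior mix, and the sickness absence rate comes from HR and not from the survey.

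It may be said that covariate adjustment belongs in an analysis plan. That would answer a silent protocol. Here the article describes both stages and names its one adjustment. That the means are unadjusted is still an inference from the absence of any covariate step, and the article says means only by way of example.

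Finally, follow-up rank and tenure are measured after randomisation, so adjusting for them could remove some effect if the intervention altered retention. Fitting without arm can also absorb a little of the effect when the mix differs by arm. Both are fair cautions. But sex, age group and tenure are not intervention targets, rank is very unlikely to be changed by the intervention, and the unadjusted analysis can be shown alongside.

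**Conclusion.** The point holds as a cheap improvement, not as a serious flaw. The stated analysis leaves the primary contrast open to an arm-specific change in respondent mix, and the variables that would remove the measured part of it are already collected. Under the assumptions in the working (20% leader share, 70% response equal across ranks at baseline, rank gap 0.5 to 1.0 SD, change confined to leaders in one arm), the bias is about 0.02 to 0.06 SD, or 3 to 13% of the target, and type I error is about 5 to 7%. A larger bias needs a lower starting response or further shifts in junior or control response. The documents do not show that any differential shift will occur. The gain in precision is a side benefit of about 1 to 5% of the standard error. The sample size is unaffected.

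**What to change.** Keep the two-stage, station-level analysis and change stage 1:

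- Within each wave, regress each survey outcome on rank group, sex, age group and length of employment, without arm. Carry the station mean residuals to the subtraction and the two-sample test.
- For the measure limited to Sergeants and above, omit the leader/junior rank term.
- Report response by rank group, arm and wave, so that any differential shift is visible.
- Keep the unadjusted station means as a sensitivity analysis.

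Follow-up in the first stratum is already being collected, so the adjustment should be fixed before outcomes are compared by arm.

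The cost is a little more programming and a category for respondents who do not state a covariate. No new data are needed. Two limits should be acknowledged: follow-up rank and tenure are measured after randomisation, and bias from unmeasured reasons for responding remains.

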**Methods/design:**

The intervention was designed collaboratively with Victoria Police based on a mixed methods pilot study, and combines multi-session leadership coaching for the senior officers within stations (e.g., Sergeants, Senior Sergeants) with tailored mental health literacy training for lower and upper ranks. Intervention effectiveness will be evaluated using a two-arm cluster-randomised trial design, with 12 police stations randomly assigned to the intervention and 12 to the non-intervention/usual care control condition. Data will be collected from all police members in each station (estimated at >20 per station). Psychosocial working conditions (e.g., supervisory support, job control, job demands), mental health literacy (e.g., knowledge, confidence in assisting someone who may have a mental health problem), and mental health will be assessed using validated measures. Organisational outcomes will include organisational depression disclosure norms, organisational cynicism, and station-level sickness absence rates. The trial will be conducted following CONSORT guidelines. Identifying data will not be collected in order to protect participant privacy and to optimise participation, hence changes in primary and secondary outcomes will be assessed using a two-sample t-test comparing summary measures by arm, with weighting by cluster size.

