### Power and sample size

Sample size was calculated taking into account the cluster design (Table 1). Effect size estimates for mental health literacy outcomes were based on observed significant changes in the primary outcome of mental health knowledge in previous randomised, controlled intervention studies [18, 20]. This is based on a scaled ‘quiz’ score and was the best available measure of workplace mental health literacy. We estimated effect size for changes in psychosocial working conditions based on previous studies [70–72], taking into account distributional methods (which often estimate minimally important score differences as ~0.5 standard deviations [73]) plus the amount of apparent change that is likely attributable to measurement error (based on test-retest correlations over a short period of time [71, 72]).

**Table 1 Tab1:** Sample size and power calculations for mental health literacy outcomes evaluated in this randomised controlled trial taking into account the cluster design at Alpha = 0.05 and Power = 0.90

	Mean	SD	Effect size (d)	Req’d standard sample size N	ICC	Design effect	Required sample size accounting for cluster design N	Required sample size after allowing for 30 % attrition
Mental health knowledge (*n* = 423)	11.14	3.57	1.79	84	0.050	1.95	164	234
Job control (*n* = 678)	49.82	11.02	8.0	40	0.032	1.60	64	91
Psychological demands (*n* = 700)	14.85	3.73	3.9	20	0.050	1.94	39	56
Colleague social support (*n* = 712)	3.07	1.23	1.2	23	0.048	1.92	44	63
Supervisor social support (*n* = 710)	3.10	1.38	1.4	21	0.019	1.37	29	41

Cluster size was set at 20 based on the rule of thumb for cluster size of m <1/ICC, assuming average ICC ~0.05 (consistent with observed values in Table 1). The ICC was used to calculate the Design Effect sample size multiplier = 1 + (m-1)(ICC). The resulting sample size estimate was then further inflated to allow for 30 % attrition at final. The cluster size of 20 is conservative, representing the minimum size for inclusion. Many clusters/stations will likely exceed this size, thus allowing for less than 100 % recruitment into the study at baseline. Resulting sample size estimates for the intervention arm are presented in the far right column of Table 1. Based on the proxy mental health literacy outcome, we will recruit 12 clusters of >= 20 participants into each arm of the trial (n of 234/20 = 11.7, or 12 clusters per arm).

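### The main test compares unadjusted change in station means, which is generally less precise than baseline adjustment and is not the comparison for which 90% power was computed

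*Protocol article*

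**What the plan says.** The Analysis section fixes a two-stage analysis. Station means are formed before and after the intervention; "pre- and post-intervention values will be subtracted to give the mean change by cluster, followed by a two-sample test" with the station as unit. The Abstract describes the same test as a "two-sample t-test comparing summary measures by arm, with weighting by cluster size". Weighting by station size is the only adjustment the main analysis commits to. Further analyses of fidelity, reach or control-site activity are optional and depend on the process evaluation. The baseline station mean is not used as a covariate. The same section says that respondents cannot be linked across waves.

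Power and sample size sets out a calculation "taking into account the cluster design at Alpha = 0.05 and Power = 0.90". On the multiplier it says: "The ICC was used to calculate the Design Effect sample size multiplier = 1 + (m-1)(ICC". No correlation between waves and no variance of a change enters. The result is "n of 234/20 = 11.7, or 12 clusters per arm".

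**The concern.** Subtraction forces a slope of 1 on the baseline station mean. That mean is noisy: with 20 respondents and ICC 0.05 its reliability is 20 × 0.05 / 1.95 = 0.51. A change score carries sampling error from both waves and gains on the follow-up mean alone only if the two waves correlate well enough. A regression on the baseline mean estimates the slope, and so loses little when the correlation is weak.

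Two things are at stake. The plan may discard precision that its baseline survey already provides. And the 90% power attaches to a different comparison, so a reader cannot tell what power the planned test has.

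**Working it through.** **1. The plan's own figure.** Inputs for mental health knowledge (Table 1): SD 3.57, difference 1.79, ICC 0.050, m = 20, power 0.90, alpha 0.05 (taken as two-sided), attrition 30%.

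- Unadjusted n per arm = 2 × (1.960 + 1.282)² × (3.57/1.79)² = 83.6, so 84.
- Design effect = 1 + 19 × 0.05 = 1.95.
- 84 × 1.95 = 163.8, so 164; 163.8 / 0.7 = 234; 234 / 20 = 11.7, so 12 stations per arm.

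This matches the row "11.14 3.57 1.79 84 0.050 1.95 164 234". It is a comparison of two independent groups at one time point with the raw SD.

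**2. Precision in general.** With equal variance V of a station mean at both waves:

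- follow-up only: V
- change score: 2(1 − r)V
- baseline-adjusted: (1 − r²)V, times about 1.05 for estimating the slope from 24 stations (checked by simulation)

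The change score is worse than follow-up only when r < 0.5. It breaks even with adjustment when 2(1 − r) = 1.05(1 − r²), so r = 2/1.05 − 1 = 0.90. Simulated variances, change against adjusted: 0.166 and 0.131 at r = 0.5; 0.0331 and 0.0332 at r = 0.9; 0.0167 and 0.0171 at r = 0.95.

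If the two waves had wholly different respondents, r could be at most 0.51 at 20 per station, or 14 × 0.05 / 1.65 = 0.42 at 14. Overlap raises it.

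**3. Power of the planned test.** In SD units, d = 1.79/3.57 = 0.501; 20 respondents at baseline and 14 at follow-up; 12 stations per arm; equal sizes, unweighted.

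- v0 = 0.05 + 0.95/20 = 0.0975; v1 = 0.05 + 0.95/14 = 0.1179
- cov = CAC × 0.05 + overlap × within-person correlation × 0.95/20
- change variance = v0 + v1 − 2cov, tested on 22 df
- adjusted variance = 1.05 × (v1 − cov²/v0), tested on 18 df (24 − 2 − 1 slope − 3 stratum terms)
- noncentrality = d / √(2 × variance / 12)

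CAC is the correlation of the true station effect across the 12 months. Overlap is the share of follow-up respondents who also answered at baseline. The article gives neither. The second block assumes 70% overlap and within-person correlation 0.6.

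| Overlap | CAC | r | Change score | Baseline-adjusted |
|---|---|---|---|---|
| none | 0 | 0.00 | 0.716 | 0.910 |
| none | 0.5 | 0.23 | 0.823 | 0.924 |
| none | 0.8 | 0.37 | 0.891 | 0.945 |
| none | 1 | 0.47 | 0.932 | 0.962 |
| 70% | 0 | 0.19 | 0.800 | 0.919 |
| 70% | 0.5 | 0.42 | 0.912 | 0.953 |
| 70% | 0.8 | 0.56 | 0.967 | 0.978 |
| 70% | 1 | 0.65 | 0.990 | 0.992 |

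First row in full: change variance 0.0975 + 0.1179 = 0.2154; standard error √(2 × 0.2154/12) = 0.1895; noncentrality 0.501/0.1895 = 2.65; power 0.72. Follow-up only gives 0.93.

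**4. The r needed for 90%.** With 14 per station at both waves the change score needs r of at least about 0.44; with 20 at both, 0.33; with 28 at both, 0.22. The 0.44 case allows a change variance of 2 × 0.556 × 0.1179 = 0.131. At 20/14 the same limit gives cov = (0.2154 − 0.131)/2 = 0.042, and r = 0.042/√(0.0975 × 0.1179) = 0.39.

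**The case against.** The strongest reply is that no shortfall has been shown. The 0.72 combines three pessimistic settings: no stable station effect over a year, no respondent in common, and the smallest station size. The article calls 20 a conservative minimum and requires 40 sworn members per station. It reports about 70% baseline response in the first stratum, so about 28 respondents at the smallest eligible station. With 28 at baseline and 20 at follow-up and no overlap, change-score power is 0.79 at CAC 0, but 0.90, 0.96 and 0.98 at CAC 0.5, 0.8 and 1. Census surveys of the same stations a year apart should also share some respondents. All of this stands.

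Only one of the five sized outcomes is exposed. The four working-conditions rows assume 0.73 to 1.05 SD (8.0/11.02 to 3.9/3.73). Even at CAC 0 without overlap, at 20/14, change-score power is 0.98 for job control and above 0.99 for the other three. This also stands.

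A reader might infer that the change score is always the less precise choice. It is not: with 24 stations it matches adjustment near r = 0.9 and is marginally better above that. A reader might also infer bias from regression to the mean. Under randomisation the change-score test on stations is unbiased and keeps its type I error; chance imbalance at baseline affects the precision of a given allocation, not validity.

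What the reply leaves untouched is that the article's power statement does not describe its own test, and that over most of the plausible range of r a more precise analysis of the same data is available.

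**Conclusion.** The point holds as one of efficiency and consistency. The main analysis is fixed as an unadjusted change in unlinked station means, while the 90% power was computed for a follow-up-only comparison. For the mental health knowledge proxy at 20/14 respondents, the planned test's power lies between 0.72 (worst case) and about 0.99, against about 0.91 to 0.99 for baseline adjustment after paying for the slope and strata.

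The documents do not support saying that the trial is underpowered. That depends on r, which is not given: the planned test falls short of 90% if r is below about 0.44 with 14 per station at both waves (0.39 at 20/14) and meets it above that. Larger stations and the working-conditions outcomes are much less affected.

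The figures assume two-sided alpha, equal station sizes, no weighting, and the stated ranges for CAC, overlap and within-person correlation. No gain in precision from stratum is credited.

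**What to change.** - **Analysis (and Abstract):** make the primary analysis a station-level linear model of the follow-up mean on arm, the baseline mean of the same outcome and randomisation stratum, carrying over the stated weighting by station size. Keep the change-score t-test as a sensitivity analysis.
- **Power and sample size:** state that the 1.95 design effect is for a follow-up-only comparison, and report power for the chosen analysis over an assumed range of r.

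The cost is four residual degrees of freedom (one for the baseline slope, three for the four strata), leaving 18 instead of 22. No new data or stations are needed. According to Trial status, follow-up is under way only in the first of the four strata, so the change can be specified before arms are compared.

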## Methods/design

### Design of the study

A two-arm cluster RCT will be used to evaluate intervention effectiveness. The cluster level is defined by police stations. Twelve stations will be allocated to the intervention condition and 12 to a wait list control condition. This design was chosen because intervention activities to improve working conditions will be conducted at the workplace level, reflecting normal practice within the host organisation, thus precluding random assignment of individual participants to intervention or control within a given police station. The mental health literacy intervention is also directed at the station level, which is anticipated to affect knowledge, attitudes and helping behaviours across each participating station.

Due to resource limitations, particularly the small number of project field staff available for recruitment, data collection, and intervention implementation, the trial will be rolled out in four temporally-staggered strata of six stations each (sets of six randomly assigned to three intervention and three control stations): a staggered cluster design. A refined version of the intervention will be implemented in control stations by Victoria Police following the conclusion of the trial.

Ethics approval was granted by Human Ethics Advisory Group at the School of Population and Global Health at the University of Melbourne (ethics number: 1340429) and the Human Ethics Committee at Deakin University (Melbourne, Australia) (ethics number: 2014-132), as well as approval from Victoria Police. The study will be conducted in accordance with CONSORT guidelines [45].

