### Sequence generation, randomisation and allocation concealment

Randomisation to either the intervention or control arms of the trial will be at the station level. A computer-generated randomisation list stratified by region (Inner Eastern, Outer Eastern, Inner North West, and Outer North West) will be created by a trial statistician who is not an investigator in the study. Given the small number of clusters involved, there is a risk that the randomisation process would produce an imbalance between the two treatment groups; to prevent this from occurring, the randomisation procedure will be balanced by size of police stations, mean unplanned absence rate at the station level in the six months prior to the trial, and the proportion of junior to senior members in each station [45, 46]. Study sites will be enrolled and then randomised until the required number of clusters and sample size is reached. As mentioned above, we will recruit in four strata. Within each stratum, there will be three stations allocated to intervention and three allocated to wait-list control. The sequence will be generated through a computer generated list of random numbers using Stata for Windows, version 12 (StataCorp, TX, USA) with an allocation ratio of 1:1. Participating police stations will be informed of their allocation to intervention or control conditions by researchers after completion of baseline surveys. Because random allocation will be conducted for each stratum of six stations after completion of baseline surveys, researchers and participants will be blinded to allocation up to the start of the intervention period for each stratum, after which blinding is not feasible due to the psychosocial nature of the intervention.

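### Stations are randomised 3:3 within four staggered strata, but the stated test has no stratum term, so precision is lost to the extent that 12-month change differs between strata

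*Protocol article*

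**What the plan says.** Design of the study: "the trial will be rolled out in four temporally-staggered strata of six stations each". Each set of six is split between intervention and wait-list control.

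Sequence generation, randomisation and allocation concealment: the list is stratified by four named regions, and "Within each stratum, there will be three stations allocated to intervention and three allocated to wait-list control". In addition, "the randomisation procedure will be balanced by size of police stations, mean unplanned absence rate at the station level" and by "the proportion of junior to senior members in each station".

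Analysis: a two-stage approach. Pre- and post-intervention summaries are formed for each station and subtracted to give its mean change, "followed by a two-sample test comparing the summary measures by arm". A t-test with n equal to the total number of clusters is given as the example, with weighting by the number of individuals per cluster. The Abstract is firmer: outcomes will be "assessed using a two-sample t-test comparing summary measures by arm, with weighting by cluster size".

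Neither place includes a stratum term. The only other adjustments mentioned are possible later analyses of fidelity, reach and activities at control stations.

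**The concern.** When allocation is forced to be equal within strata, anything that shifts all six stations of a stratum together affects both arms alike and cannot contribute to the arm difference. A two-sample t-test estimates its error from the spread of stations within each arm, pooled over strata, and that spread still includes the shifts. The standard error is then larger than the design warrants.

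Common shifts in change are plausible here. The strata cover different regions and run in different 12-month calendar windows, and the Data collection section itself anticipates restructures, changes of key staff and other events that could affect outcomes. With 24 units of analysis, and a sample-size calculation of 11.7 rounded to 12 clusters per arm, there is little precision to give away.

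**Working it through.** **The plan's own figure.** From Table 1, mental health knowledge: difference 1.79, SD 3.57, alpha 0.05 (two-sided assumed), power 0.90.
- n per arm = 2 × (1.960 + 1.282)² × (3.57/1.79)² = 83.6, so 84.
- Design effect = 1 + 19 × 0.05 = 1.95, and 84 × 1.95 = 163.8, so 164.
- 164/0.70 = 234.3 (stated 234), and 234/20 = 11.7, so 12 clusters per arm.

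The figures reproduce. They contain no allowance for strata in either direction.

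**Inputs for the check.** Four strata of six stations, 3:3 in each, from the design sections. The four regions and the four staggered sets are taken to be the same strata; the argument needs only the 3:3 split within each set. Let ρ be the share of variance in station change that lies between strata. The document gives no value, so it is varied as an assumption. Total variance is set to 1.

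**Standard error.** The arm difference sees only within-stratum variance, 1 − ρ. Each arm has 12 stations, 3 per stratum, so the expected within-arm sample variance is (1 − ρ) + (3 × 3/11)ρ = (1 − ρ) + (9/11)ρ. The ratio of reported to true standard error (root mean square) is therefore √[1 + (9/11) × ρ/(1 − ρ)]:
- ρ = 0.1: √1.091 = 1.04
- ρ = 0.2: √1.205 = 1.10
- ρ = 0.3: √1.351 = 1.16

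The simple average of the standard error runs one to two percentage points lower, hence the ranges in the table.

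**Type I error and power.** Station changes were simulated without weights. The effect was fixed at 1.385 SD of station change, which gives 90% power with 22 df at ρ = 0. The unstratified t-test (22 df) was compared with arm plus stratum (24 − 4 − 1 = 19 df).

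| ρ | SE too large by | Type I error, unstratified | Power, unstratified | Power, stratified |
|---|---|---|---|---|
| 0 | none | about 0.05 | 0.902 | 0.896 |
| 0.1 | about 4% | 0.041 | 0.916 | 0.926 |
| 0.2 | 8 to 10% | 0.034 | 0.926 | 0.948 |
| 0.3 | 14 to 16% | 0.028 | 0.936 | 0.970 |

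Repeat runs of 60,000 and 100,000 trials agree with these powers to about 0.3 of a percentage point. The stratified test held its type I error at about 0.05 throughout. Both power columns rise with ρ because total variance is held fixed, so within-stratum variance shrinks; the comparison is across each row. At ρ = 0 the non-central t distribution gives 0.900 with 22 df and 0.896 with 19 df.

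**With weights.** The planned test is weighted, so stratum shifts cancel only approximately. With station numbers assumed to range from 20 to 60, power was 0.917 against 0.943 at ρ = 0.2, and 0.930 against 0.966 at ρ = 0.3. Weighting does not remove the gap.

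**How large could ρ be?** With ICC 0.05 and 20 respondents per station, and treating the two anonymous surveys as independent samples, sampling noise in a station's change is 2 × 0.95/20 = 0.095 in units of individual variance. True station change contributes 2 × 0.05 × (1 − c), where c is the assumed correlation of a station's true level over the year. True change is then 0.100/0.195 = 51% of the variance at c = 0, 0.050/0.145 = 34% at c = 0.5, and 0.020/0.115 = 17% at c = 0.8. If repeat responders halve the noise to 0.0475, these become 68%, 51% and 30%. Strata can account for only part of that part, which points to the lower rows of ρ.

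**The case against.** The strongest reply is that nothing is broken. Omitting stratum leaves the estimate unbiased and pushes type I error down, not up. In every row of the table the planned test still has power of at least 0.90, and stratifying adds about one to three points. The outcome is a change score, so stable regional differences are already gone and only differences in change remain. On the protocol's own ICC and cluster size, large values of ρ are hard to reach. All of this stands, and it limits the point to efficiency.

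It can also be said that the Analysis section gives the t-test only as an example, and that a condensed article leaves covariates to an analysis plan. This mitigates but does not dispose of the point. The Abstract names the t-test without qualification, and test, unit, n and weighting are all stated. This is a stated method that does not follow the randomisation, not an omitted detail.

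Three stronger readings are tempting and not supported.
- A reader might infer that the standard errors are too large as a matter of course. They are so only if ρ is above zero, and the document does not show that.
- A reader might take the fine-tuning of local activities, described under Process evaluation, as evidence of stratum differences that adjustment would absorb. Those changes reach intervention stations only, so they make the effect vary by stratum and do not shift both arms. When such variation was simulated at 5%, 10% and 20%, power was 0.902 against 0.899, 0.905 against 0.904, and 0.910 against 0.911: stratum adjustment gained essentially nothing.
- A reader might want the three balancing variables in the main model, or a permutation test over permitted allocations. No gain was computed for either. The covariates would take the residual df from 19 to 16, and the balancing algorithm is not described, so the permitted set cannot be built from this document.

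**Conclusion.** The point holds as a mismatch between randomisation and analysis that can only cost precision. The direction is firm: with 3:3 allocation in each stratum, leaving stratum out makes the test conservative whenever strata differ in their change. The size is not firm. It rests on ρ, which is assumed, and most of the figures come from unweighted simulation. Over ρ from 0.1 to 0.3 the standard error is about 4% to 16% too large and one to three points of power are given up; at zero there is no loss. It is a recommended, low-cost improvement. It should not be presented as a validity error, nor as grounds to doubt a positive result.

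**What to change.** In the Analysis section and the Abstract, replace the two-sample t-test with a station-level linear regression of mean change on arm plus stratum (four levels, fixed effect), keeping the planned weights. Report the stratum-adjusted difference and its confidence interval, on 19 df, as the main result.

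Adjustment for station size, prior absence rate and junior-to-senior ratio can be listed as an optional sensitivity analysis. So can a restricted permutation test, once the balancing algorithm is written down.

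The cost is a change of wording and three degrees of freedom (22 to 19), worth about half a point of power if strata turn out not to differ. No further data are needed. Trial status reports that follow-up was under way only in the first stratum, so the change can be dated and recorded before most outcome data exist.
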